## Abstract

**Background:**

Preterm infants are high risk for delayed neurodevelopment. The main goal is to develop a program of early intervention for very preterm infants that allows families to apply it continuously at home, and quantify the results of early parental stimulation on improvement of cognition and motor skills.

**Methods:**

Randomized clinical Trial including inborn preterm infants with gestational age less than 32 weeks or birth weight less than 1500 g at 48 h after birth. Eligible for begin the intervention up to 7 days after birth. Study Protocol approved by the Brazilian national Committee of ethics in Research and by the institutional ethics committee.

Intervention group (IG): skin-to skin care by mother (kangaroo care) plus tactile-kinesthetic stimulation by mothers from randomization until hospital discharge when they receive a program of early intervention with 10 parents’ orientation and a total of 10 home visits independently of the standard evaluation and care that will be performed. Systematic early intervention program will be according to developmental milestones, anticipating in a month evolutionary step acquisition of motor and / or cognitive expected for corrected age. Active comparator with a Conventional Group (CG): standard care according to the routine care of the NICU and their needs in the follow up program. Neurodevelopment outcome with blinded evaluations in both groups between 12 and 18 months by Bayley Scales of Infant and Toddler Development third edition and Alberta Motor Infant scale will be performed. All evaluations will be conducted in the presence of parents or caregivers in a safe room for the child move around during the evaluation.

**Discussion:**

If we can show that a continuous and global early intervention at home performed by low income families is better than the standard care for very preterm infants, this kind of program may be applied elsewhere in the world. We received grants by Bill and Melinda Gates Foundation, DECIT, Cnpq and Health Ministry. Grand Challenges Brazil: All Children Thriving.

**Trial registration:**

The study was restrospectively registered in ClinicalTrials.gov. in July 15 2016 (NCT02835612).

## Background

Born prematurely and its consequences cause major impact on society and health indicators of population. According to the 2012 “Born Too Soon: The Global Action Report on Preterm Birth” of the World Health Organization, Brazil is ranked 10th among the countries with the highest number of preterm live births and 16th in deaths due to complications of prematurity [1]. The data from 2012 indicate that approximately 3 million babies are born in Brazil each year, 350,000 of whom are born with less than 37 weeks of gestation, and prematurity index is higher in the last three years, including preterm very low birth weight infants (gestational age less than 32 weeks and birth weight less than 1500 g). More than half of the preterm infants with birth weight less than 1500 g and gestational age GA of 23–33 weeks born in public university centers of Brazilian Neonatal Research Network died or were discharged with severe pulmonary, neurological or ophthalmological complications [1, 2].

Assistance in the delivery room with effective resuscitation is important for high risk infants and among the survivors is imperatives a continuous follow up clinic program. Follow up program is a continuous of neonatal and perinatal care and should provide conditions to monitor growth, development and common morbidities with a multidisciplinary team able to fully assess the child and the caregivers, parents, all family and school [3, 4]. According Cochrane Review there is a great deal of heterogeneity between studies due to the variety of early intervention programs and gestational ages included in these studies [5].

Despite of those evidences, the role of the family applying those programs at home is not well studied especially in social deprived environments. It is possible that a care process modified by households is beneficial for neurodevelopment outcome, in both; cognitive and motor skills.

Any early intervention for high risk preterm infant must focus in the parents-infant relationship, environment and behavior attitudes in order to reduce stress among parents of prematurely born children and improves neurovelopment outcome their children during childhood [6]. So, our main hypotheses is that a continuous global early stimulation done by parents at home for very preterm infants is better than the traditional one, and it can be offered to many very preterm infants even in poor environments.

To develop a program of early intervention for very preterm infants that allows families to apply it continuously at home is the main goal. An additional objective of this study protocol is to quantify the results of early stimulation on improvement of cognition and motor skills.

There are several intervention programs involving multisensory and motor stimulations such as, gym, auditory, visual, vestibular and tactile stimulations [7–9]. Developing countries must allocate their resources according to their conditions. Preterm infants require several different professionals to take care of them, and many places do not have enough people to take care of all preterm infants.

` We propose a randomized clinical trial to evaluate a continuous program of early intervention involving very preterm infants’ families in their first 12 to 18 months of life taking the chance of their neuronal plasticity during this period.

## Methods

The study has been designed in accordance with the SPIRIT 2013 statement and we are still collecting data and recruiting the patients. The study setting is Hospital de Clinicas de Porto Alegre, Brazil. Hospital de Clinicas de Porto Alegre, an academic hospital, has more than 3800 deliveries /year and the NICU has 120 to 150 very preterm infants admitted yearly. Obstetric Unit of the hospital has 150 deliveries with gestational age ≤ 32 weeks per year. There is a 20 bed level III Neonatal Intensive Care Unit with conventional and high frequency ventilation, nitric oxide therapy, bed cranial and cardiac echocardiography available any time during the day, 3 on call board certified Neonatologists the whole day. There is also a team available for birth assistance anytime during the day. All included preterm infants and their parents will be followed during neonatal period. There is a follow up clinic that take care of preterm infants with gestational age less than 32 weeks or those with birth weight less than 1500 g birth weight independently of their gestational age cared at our NICU evaluating periodically their growth and neurodevelopment outcomes and forwarding to specialized professionals according to their necessity.

Eligibility criteria: Randomized Clinical Trial including inborn preterm infants with gestational age less than 32 weeks or birth weight less than 1500 g when they complete 48 h after birth. Our inclusion criteria are based in a critical cut off point of gestational age and birth weight according different studies [3, 4, 10, 11]. We decided to approach our study in a group of preterm infants with gestational age less than 32 weeks or those with birth weight less than 1500 g independently of their gestational age. Exclusion criteria: neonates that death prior 48 h after birth with major congenital malformations or inborn errors of metabolism, STORCH complex infections, HIV, or autoimmune conditions.

The study was restrospectively registered in ClinicalTrials.gov. in July 2016 and the first participant was enrolled in the study in February 2016. Protocol record 150,606 has been reviewed and public available on ClinicalTrials.gov. Identifier: NCT02835612.

Interventions: Written informed consent was signed by the parents of all preterm infants that filled inclusion criteria in the study protocol. When they complete 48 h of life they are sequentially randomized. The intervention is planned to start on the 7th day of life according the randomization in two arms:

Conventional group (CG): Standard care, according to the routine care of the NICU: skin-to skin care by mother, kangaroo care, and breast feeding policy. After discharge they are referral for a traditional follow up clinic taking care of the demands according to their necessity; with motor, and cognition evaluations and interventions according to their needs.

Intervention group (IG): Skin-to skin care by mother, kangaroo care, breastfeeding policy plus massage therapy are made by the mothers until hospital discharge. After discharge, they receive standard follow up care plus orientation for a continuous global simulation at home. Early intervention will be according to developmental milestones, anticipating in one month evolutionary step acquisition of motor and / or cognitive expected for corrected age. Besides that, we have a total of 10 home visits promoting guidance and supervision sessions. After each appointment, there is one home visit. A number of ten orientations appointments and ten home visits must be completed for each subject included in the IG. A complete description for each group is detailed below:

Conventional group: Our NICU has worked with Kangaroo mother care (KMC) as the practice of skin-to-skin contact since 1990 for all very low birth weight infants that parents consent to participate and their infants have clinical conditions. We have guidelines including staff knowledge and adequate training with available information to assist and support in developing best-practice guidelines and protocols for implementation this practice. During KMC, the infant, clad in a diaper and cap, is held in an upright prone position against the bare chest of the parent (most often the mother) and covered with clothing and/or a blanket. The duration of skin-to-skin contact is usually one hour per session, with cardiorespiratory and temperature monitoring of the infant during all this time. Although most often provided for stable preterm infants who do not require assisted ventilation, we have offered to preterm infants as young as 26 weeks’ gestational age and birth weight 600 g or more who require respiratory support. We have promoted exclusive breastfeeding. Infants have been discharged home regardless of weight as soon as their mother understood how to care for and feed her infant [12].

In developing countries, KMC for preterm infants has been shown to reduce mortality, severe illness, infection, length of hospital stay and improved mother-infant attachment [13].

After discharge all preterm infants (birth weight < 1500 g) born at the Hospital de Clínicas de Porto Alegre (HCPA) are routinely referred to the Neonatology outpatient clinic for monthly follow-up visits until 6 months of corrected age (CA), bimonthly from 7 up to 12 months corrected age, and every 3 months thereafter until age 24 months, according to routine hospital practice.

A multidisciplinary team is required to form a follow up clinic [3, 4, 10]. Our follow up clinic is coordinated by a neonatologist that understands the infant as a whole. The follow up multidisciplinary team is presented in Table 1.

**Table 1 Tab1:** Multidisciplinary team in the follow up program

Member of the team	Role in the team
Pediatrician/Neonatologist	Coordination, evaluate growth and screening of development, take care of the general clinical medical problems
Psychologist	Evaluate neurodevelopment using scales, psychological problems, parental infant bonding
Pediatric Neurologist	Manage seizures, cerebral palsy, swallowing problems
Ophthalmologist	Evaluation of Retinopathy of Prematurity (ROP), visual acuity, strabismus
Ear, nose and throat doctor	Evaluation and management of hearing problems
Nutritionist	Management of growth failure
Speech Therapist	Speech problems and swallowing problems
Nurse	Immunization and Hygiene control

During the appointments, feeding orientations, weight gain, general health/illness and infections are recorded. A 24 h dietary recall is administered at each visit to assess feeding routines, use of formula, breast milk, and family food preferences. Routinely feeding orientations have been offered according their needs (exclusive breastfeeding or mixed feeding or infant formula; nutritional requirements according their corrected age). Recurrent admissions during the first year of life, anthropometric parameters (weight, head circumference, body mass index, and length at 6, 12 and 18 months of corrected age (z scores plotted on WHO growth charts), and results of routine tests performed at 1 year of corrected of age are systematically recorded.

Patients will have their motor neurodevelopment evaluated by AIMS (Alberta Infant Motor Scale at 6 and 12 moths of CA) and forwarding to specialized professionals according to their necessity. The scale was translated and adapted to the Portuguese language, being quick and easy to application. The reliability and reproducibility showed satisfactory values [14]. Applications of the Bayley Scales, cognition, language and motor (BSDI- III, Bayley Scale Development Index, version III), by qualified and trained professional will be performed at 12 months CA for all infants [15].

The examiner is able to distinguish, by means of comprehensive and standardized protocols for neurological development, developmental scales and tests between the normal biological variation and the deviant development. The clinical approach has the great advantage of being easily repeated, obtaining developmental trajectories that can lead to neurological disorders being suspected in both arms [16] .

**Intervention group (IG):** We have implemented a program of early, continuous and global intervention with parents’ orientation independently of the standard evaluation and care that will be performed for preterm infants. In NCIU eligible preterms receive skin-to skin care by mother, kangaroo care, breast feeding policy plus the tactile-kinesthetic stimulation by mothers from randomization and after preterm’s are clinically stable (7 days after birth) until hospital discharge. Intervention performed exclusively by the mothers is based on studies regarding the application of skin stimulations and passive exercises in preterm infants [9, 17, 18].

Previously we performed the same early intervention during NICU stay as follow [19]: Mothers are taught to perform a tactile and kinesthetic stimulation four times a day with an interval of 6 h during 15 min. The tactile stimulation is done with two or three fingers with a gently pressure three times in one direction and in the opposite direction on the temporal, frontal, periorbital, nasal and perilabial regions of the face; the external side of the upper and lower limbs. The kinesthetic stimulation was performed with passive [19]. Mothers of the IG are instructed to observe the newborns’ tolerance signs to avoid excessive stimulations.

During NICU stay researchers of our team have had regular meetings with mothers included in IG every 48 h to assure that they are doing the intervention as instructed and to check the parental bond [20]. In previous publication we demonstrated that massage therapy by mothers combined to skin-to-skin care during neonatal hospital stay improved neurodevelopment outcome at 2 years corrected age [21] .

After discharge, preterm infants have standard care of a traditional follow up clinic taking care of the demands according to their necessities and they receive orientation for a continuous global simulation at home besides the usual appointments to the follow up clinic, monthly in the first semester corrected age and bimonthly in the second semester until 12 months corrected age and every 3 months thereafter until age 24 months corrected age. Our study protocol has offered ten additional appointments for systematic orientation for a continuous global simulation at home; and ten home visits during the first 18 months corrected age.

Follow up appointments, home visits, intervention during follow up program and all systematic orientation for early intervention have been done according to developmental milestones, anticipating in a month evolutionary step acquisition of motor and/or cognitive expected for corrected age. The theoretical neurodevelopmentalist referential of the main periods for the acquisition of developmental landmarks have been used [22].

During the sessions the patient should be well fed, have slept his nap and comfortable. Parents are learning to read your preterm’s behavior and respect their needs. We have distributed flyers with techniques and science-based activities to be applied systematically and sequentially at home. Parents have one flyer per appointment; a total of 10 flyers with orientations will be distributed for each subject of IG. Each patient will have a complete book of orientations in the end of the study.

In IG, during first six months corrected age, mother, father and / or corresponding caregivers have been received six flyers: simple guidelines to encourage large motor skills, fine and cognition and some toys.

From discharge up to three months corrected age: Sitting next to their children parents must place them on their stomach on the floor, being sure that their face, mouth, and nose is not covered, using a foam roller to position. Although tummy time is very important, preterm infants should also have time playing on their backs; so stimulation is also performed with the child in the position lying in bed or prone position and/or during bath; a number of three detailed guideline orientations is offered for each included family. Folders with detailed illustrations are offered to parents:

Gross and fine motor stimulation: Crossing arms and relaxation movements (play in the bath for 5 to 10 min, beating hands and feet in water, rubber animals). To make gymnastic movements with flexion and passive extension of the upper and lower limbs; in order to support themselves on the upper limbs in the prone position and to acquire the expected rolling ability.

Cognitive stimulation: Getting close and speak slowly, singing low. Use a mobile to look up, black and white gloves to put in the hands’ mother to play and the child turn your head 180 °C.

Material’s kit for the first, second and third appointments: foam roller to position, rubber animals (3 each/child), black and white woolen gloves, one for each mother / parent intervention group; colorful rattle without light and colored mobile.

From 3 up to 6 months corrected age: a number of three detailed guidelines have been offered to mother/father to stimulate their preterm infant presenting different opportunities to explore, develop skills and abilities in a natural way.

Gross and fine motor stimulation: parents are advised to put back the child to a large plastic ball holding child’s thighs them. Roll the ball slowly forward and back, side to side in order to prepare for the sitting position and obtain equilibrium. To raise the child lying on his back with a nearby color mobile tummy, arms open and extended by the mother holding the child’s hands, showing him that the child should try to catch with their feet; learning to ride. Teach touch objects (sponge rough on one side and the other foam) with different textures (soft, hard, and rough), describing the characteristic touch (stimulates cognition).

Cognitive stimulation: listening to music, singing and reading simple words and short sentences. After the bath, while dry parts of the body with a towel; the mother is guided to speak the body parts that she is drying up; mother says: the foot, the hand, arm and so on…speaking slowly with the child. In the mirror, she shows and names: eyes, mouth, nose, both mother and child, for it to become aware of their individuality. Social interaction is emerging in this ages and need to be stimulated.

Material’s kit for the fourth, fifth and sixth appointments: Colorful rattle with light, plastic large ball, small unbreakable mirror, books with stories, rag doll or cloth toy. Eco sponges commercial home kitchen wash dishes.

From 7 up to 12 months corrected age: study protocol has two detailed guidelines and appointments. Simple guidance for parents has been strengthened in this phase: “Help your child learn to locate things by listening: show her the toy, then put it behind your back and activate the sounds. Do this several times to see if she will crawl to you to find the source of the sound”.

Gross and fine motor stimulation: gymnastics intends to tone the muscles in order to prepare for the first sitting position and then standing without support, to walk independent. Using a large plastic ball (the ball should not be too full) the mother is oriented to hold the child against him, one hand holding his knees thereof and the other the chest. Using the floor with EVA material for the child to have displacement space, the parents play small colored balls twice a week talking about the game (action/reaction). To stimulate fine motor, is guided to offer magazines to be torn by the child, showing how to do it quietly. Once torn into several pieces, teach to make a paper ball with the pieces and play ball with the child.

Cognitive stimulation: In the mirror, mother shows different colored pieces (balls, books) talking slowly each color and numbers, using gestures when she talks to child, linking her actions to her words**.**

From 8 months of corrected age, display and nominate the body parts: head, belly, hand, foot, mouth, nose, eyes. Read books and show the animal pictures, repeating the name of each figure well paused and with the mouth wide open. Material kit for the seventh and eighthappointments: Small colored balls of non-toxic rubber (number = 6). EVA Material (100 cm × 100 cm).Toy fit, action/reaction toy, colored cubes with all geometric forms (one for each subject included in IG).

From 13 up to 18 months corrected age: study protocol has two detailed guidelines and appointments. Parents have been learned to speak and to teach the child mimics what other people do, babbling syllables like words, demonstrating what she wants with gestures; they need to encourage the child to get physically involved with the toy to strengthen muscles and confidence.

Gross and fine motor stimulation: reinforced by the researchers that the game and the play are the best way to stimulate a child. Using a large plastic ball, the mother/father is oriented to tilt the child’s chest to the ball until he/she can put the hands to make a little effort to get up; following the stimulation, the child learns to roll the ball, causing the release of both hands. It is important to advise the mother to release the child gradually hip.

Cognitive stimulation: parents are advised to read a book every day, and when they read these books, talk to child about these feelings. Get him to show how his face looks when he is mad, afraid, etc.… Talk repeatedly reinforcing each child’s achievement is very important all the time.

Material’s kit for the ninth and tenth appointments: Wooden poles with 60 cm in size each, two for each subject in the intervention group; four books with drawings of animals and objects and one case with 12 crayon colors for each subject.

All these activities must not use more than 15 min and they must seem games. Three times / week (alternating with gross and fine motor stimulation) and daily cognitive stimulation are recommended for IG plus conventional care according their needs. All parents will receive the same material kit for stimulation use that is sponsored by Bill and Melinda Gates Foundation. We have be done systematic orientations for cognitive stimulation, fine and gross motor, totaling 10 appointments and 10 home visits promoting guidance and supervision sessions. Systematic orientations will be delivered to parents in all medical appointments at follow up clinic. In the explanatory material for parents each description refers to an activity is a representative figure of the same proposal activity in order clearly to communicate for parents.

The aim of home visits is to evaluate the comprehension of the orientation and to be sure that the intervention has been done by families, a strategy to improve adherence to intervention protocol. During home visits pictures are taken, there is an explanation of the clinical relevance of the study and questions are promptly answered by the multidisciplinary team.

There is a multidisciplinary team involved in the whole study and we will have a critical view of the intervention impact (final evaluation) in both; conventional and intervention groups (Table 1).

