Many studies have been focused only in motor development after early intervention [7]. Recent neuroplasticity literature suggests that intensive, task-specific intervention ought to begin as early as possible and in an enriched environment, during the critical period of neural development. Active motor interventions are effective in some populations. However, the effects of those active motor interventions on the motor outcomes of infants with Cerebral Palsy (CP) have been researched only in a pilot study [24]. Goals - Activity - Motor Enrichment): protocol GAME, was used in that pilot study [25]. The cognition is very poor evaluated after early intervention programs. Recently, the effects of the Teach-Model-Coach-Review instructional approach on caregivers’ use of four enhanced milieu teaching (EMT) language support strategies and on their children’s use of expressive language were examined and the results were positive, but preliminary evaluated [26].

To explore the effect-size of this early intervention program in offer conditions to parents stimulate their preterm children we will provide guidelines for parental bonding. The EAS is a set of scale designed to assess the ability of parents and child to share a healthy emotional connection, therefore addressing the adults and the child relationships [27]. An innnovative and essencial outcome will be evaluate if parents can learn how to support their child’s development of motor and cognitive processes by receiving specialized and multidisciplinary skills training.

The study protocol needs to be share with healthcare professionals in order to use the same approach in other countries with high risk situations for poor neurodevelopment outcome. Thus, if we can show that a continuous and global early intervention at home performed by low income families is better than the standard care for very preterm infants, this kind of program may be applied elsewhere in the world. It can be expanded for the whole preterm population in order to improve their neurodevelopment outcome.

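### The two arms differ by a NICU-plus-home package, but the main hypothesis and planned conclusion credit stimulation at home, a part the design cannot isolate

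*Protocol article*

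**What the plan says.** **What is claimed.** The Background gives the main hypothesis: "a continuous global early stimulation done by parents at home for very preterm infants is better than the traditional one". The closing paragraph of the Discussion, and the Discussion part of the Abstract, make wider use of the programme conditional on one finding: "if we can show that a continuous and global early intervention at home performed by low income families is better than the standard care".

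**What is compared.** Under Interventions in Methods, infants are allocated "according the randomization in two arms". In the NICU the conventional group receives "Standard care, according to the routine care of the NICU: skin-to skin care by mother, kangaroo care, and breast feeding policy". For the intervention group the text reads: "Skin-to skin care by mother, kangaroo care, breastfeeding policy plus massage therapy are made by the mothers until hospital discharge". After discharge both groups have the standard follow-up clinic, and the intervention group also has "ten additional appointments for systematic orientation for a continuous global simulation at home; and ten home visits during the first 18 months corrected age".

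**What is said about the NICU part.** The Intervention group description says the team has used the same NICU intervention before. A paragraph later it reports that "massage therapy by mothers combined to skin-to-skin care during neonatal hospital stay improved neurodevelopment outcome at 2 years corrected age". The two statements carry different citations.

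**The concern.** The claim names one component; the randomised contrast contains two. The protocol itself reports a developmental benefit at 2 years corrected age from maternal massage with skin-to-skin care during the hospital stay. That is later than this trial's primary assessment at 12 to 18 months. A difference between the arms could therefore reflect the NICU stimulation, the home programme, or both.

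The Abstract and Discussion would read a positive result as showing that intervention at home beats standard care and could be taken up in other countries. A service might then adopt the appointments, home visits and material kits without the NICU part. The trial would not have tested that combination.

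**Working it through.** **Step 1. What each arm receives** (Methods: Interventions, Conventional group, Intervention group, randomisation paragraph).

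| | Conventional | Intervention |
|---|---|---|
| Randomisation | once, at 48 h | once, at 48 h |
| Skin-to-skin care and breastfeeding policy in NICU | yes | yes |
| Maternal tactile-kinesthetic stimulation in NICU, planned from day 7 to discharge | no | yes |
| Standard follow-up clinic | yes | yes |
| Ten orientation appointments and ten home visits | no | yes |

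Of the four possible combinations of NICU stimulation (no/yes) and home programme (no/yes), the trial observes only no/no and yes/yes. No second randomisation at discharge is described.

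**Step 2. What the difference estimates.** Let D be the mean difference between arms at 12 to 18 months, d the effect of the NICU part without the home programme, and h the effect of adding the home programme in infants who had the NICU part. Then

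D = d + h, so h = D − d.

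The trial estimates D. It has no data on d, and the documents give no figure for it. If d is 0%, 50% or 100% of D, the home share is 100%, 50% or 0%, and the data look the same in each case. This holds for any two-component package. What makes it matter here is that the protocol claims h and also reports earlier evidence suggesting that d may not be zero.

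**Step 3. The plan's own figure.** Sample size in Methods gives 84 infants (42 per arm), a 3-point difference, 5% significance and 80% power. No SD is stated, so 84 cannot be reproduced directly. Solving backwards with a two-sided test and a normal approximation:

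SD = 3 / [(1.960 + 0.842) × √(2/42)] = 3 / (2.802 × 0.2182) ≈ 4.9 (about 5.5 if one-sided).

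**Step 4. Illustration.** Assume SD 4.9, 42 per arm and a home programme with no effect (h = 0). The standard error is 4.907 × 0.2182 = 1.071. The chance of a significant difference from the NICU part is Φ(d/1.071 − 1.96) + Φ(−d/1.071 − 1.96).

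| NICU effect d (points) | Chance of a significant result with h = 0 |
|---|---|
| 0 | 5% |
| 1 | 15% |
| 1.5 | 29% |
| 2 | 46% |
| 3 | 80% |

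A larger SD lowers these figures. For d = 3 the chance is about 28% at SD 10 and about 15% at SD 15. The SD and the values of d are assumptions; Steps 1 and 2 do not depend on them.

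**The case against.** The strongest reply is that this is a package trial and the protocol says so. The Abstract's Methods define the intervention group by both parts. The quantitative objective in the Background refers to early stimulation in general, and the Outcomes section to early systematic intervention. Objective 1 in Table 2 includes massage by mothers from the neonatal period. The Discussion opens with a programme that runs from the NICU stay to after discharge. Testing a package is legitimate, and not isolating its components is no error in itself. All of this stands. It also shows where the fault lies: the main hypothesis and the planned conclusion do not match the contrast that the rest of the document describes.

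Three stronger readings are tempting, and the documents support none of them.

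- *That massage alone was shown to improve development.* The protocol says massage combined with skin-to-skin care and does not give the earlier comparator. If those controls had no skin-to-skin care, that care could have produced the benefit, and here both arms receive it.
- *That a NICU effect is certainly present at 12 to 18 months.* The statement about the same NICU intervention and the statement about the 2-year benefit have different citations, and the protocol does not say that both concern one study. Carry-over is plausible, not established.
- *That the NICU part is enough to explain a positive result.* That would need the size of the earlier effect, which is not given.

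The percentages in the illustration are also open to challenge, because they rest on an SD inferred from the sample size.

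**Conclusion.** The point holds as a mismatch between claim and contrast. The trial can validly estimate the effect of the combined NICU-plus-home programme against standard care. It cannot support the statement that stimulation at home is better than standard care, because the difference may include a NICU effect of unknown size that the design cannot separate.

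A reader might infer that the trial cannot answer its question at all. That goes too far: randomisation protects the package comparison, and only the attribution to the home part fails.

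The conclusion about attribution rests only on the description of the arms. That carry-over is a realistic possibility rests on the protocol's brief report of the earlier result. The size of the problem cannot be narrowed from the documents: the home share of any difference may lie anywhere from 0% to 100%, and it could fall outside that range if the two parts work in opposite directions.

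**What to change.** Change the wording in three places and add one statement.

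- **Background, main hypothesis:** state it as a parent-delivered programme, consisting of maternal tactile-kinesthetic stimulation in the NICU followed by the home programme, compared with standard care.
- **Abstract (Discussion) and closing paragraph of the Discussion:** make the conditional conclusion about this combined programme, not about intervention at home.
- **Discussion, added limitation:** say that a difference between arms cannot be attributed to the home component, because the NICU component is a possible full or partial explanation, and cite the team's earlier result as the reason.

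No patient, visit or analysis changes. The only cost is a narrower claim.

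A redesign is not proposed. Isolating the home part would need equal NICU care in both arms, randomisation at discharge or a factorial layout, and recruitment is already under way. It would also need more infants. With the SD inferred above, the total scales as 84 × (3/h)². A home effect of 2 points needs 84 × 2.25 = 189, or 190 in equal arms, and one of 1.5 points needs 84 × 4 = 336. Both are before any allowance for loss, against a planned total of 100 that includes it.
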